### Sample size

The trial will use a Bayesian group sequential design^18–20^ to monitor recruitment with interim analyses planned for every 50 participants completing the 4-month follow-up. Each of the primary outcomes will be modelled according to the analysis plan (see the Analysis section), and coefficients for dummy variables representing presence/absence of each component at each follow-up interval will be assessed for effect, harm and futility with respect to each outcome. We let ß_k, l, i_ represent the regression coefficient for component *k*, at time *I*, for outcome *i* and D all the data currently accumulated, then the target criteria will be:

Effect (fruit/veg. and physical activity): p(ß_k, l, i_ > 0 | D)>97.5% and p(ß_k, l, i_ > 0.10 | D)>50%.Harm (fruit/veg. and physical activity): p(ß_k, l, i_ < 0 | D)>97.5% and p(ß_k, l, i_ < -0.10 | D)>50%.Effect (alcohol and smoking): p(ß_k, l, i_ < 0 | D)>97.5% and p(ß_k, l, i_ < -0.10 | D)>50%.Harm (alcohol and smoking): p(ß_k, l, i_ > 0 | D)>97.5% and p(ß_k, l, i_ > 0.10 | D)>50%.Futility (all outcomes): p(−0.10 < ß_k, l, i_ < 0.10 | D)>95%.

Outcomes analysed using normal regression will be standardised when checking the above criteria. For the effect and harm criteria, we will use a standard normal prior for dummy covariates (mean=0, SD=1.0), and a slightly wider prior will be used for the futility criterion (mean=0, SD=2.0). The criteria should be viewed as targets, thus at each interim analysis we will evaluate each criterion and decide if we believe that recruitment should stop or continue. We will continue recruitment until one criterion is fulfilled for each component, for each outcome, at each follow-up interval. We will consider removing factors from the trial if the harm criteria are fulfilled for a component on all outcomes. We will not remove factors for which the effect or futility criteria are satisfied, as collecting additional data will facilitate reducing uncertainty regarding interaction effects. Note that we are estimating each component’s effect on each outcome, thus we are not a priori excluding any combination. If a component is ineffective with respect to a specific outcome, then this will be captured by the futility criteria, and will also be reported as a finding.

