While the final sample size is not determined a priori, we conducted a series of simulations with effect sizes at the minimal value of the above criteria (0.1 Cohen’s d for fruit/veg and physical activity, 1.1 incidence rate ratios for alcohol and 1.1 ORs for smoking). Simulations suggested that approximately 1500–2500 participants will be necessary to recruit. However, the criteria will decide, not the simulations. Despite having more conditions than in a traditional two-arm trial (in this case 64 conditions), the factorial design is fully powered for each contrast.^17^ This can be understood by observing that half the study population are given access to each individual component (see online supplemental appendix table 1 in appendix B), thus the other half creates a contrast (a type of control).

Note that the Bayesian approach allows us to make unlimited looks at the data without worrying about multiplicities and error rates, as would be necessary using a frequentist approach.^43^ Also, since no fixed effect size is prespecified, we reduce the risk of stopping recruitment both too early and too late.^20^

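### The projected 1500–2500 participants fits one coefficient meeting a criterion, not the stated rule that recruitment continues until all 60 component-by-outcome-by-time cells have met one

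*Protocol article*

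**What the plan says.** The Sample size section of the protocol article sets three kinds of target on each regression coefficient.

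- Benefit for diet and activity: "Effect (fruit/veg. and physical activity): p(ß_k, l, i_ > 0 | D)>97.5% and p(ß_k, l, i_ > 0.10 | D)>50" per cent.
- Benefit for alcohol and smoking is the mirror image: "Effect (alcohol and smoking): p(ß_k, l, i_ < 0 | D)>97.5% and p(ß_k, l, i_ < -0.10 | D)>50" per cent. Harm reverses the signs.
- Futility: "Futility (all outcomes): p(−0.10 < ß_k, l, i_ < 0.10 | D)>95" per cent.

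The effect and harm checks use a "standard normal prior for dummy covariates (mean=0, SD=1.0"). The futility check uses a prior SD of 2.0. Looks occur after every 50 participants who complete 4 months. Recruitment goes on until every pairing of component and outcome has satisfied one of the criteria at each follow-up, although the criteria are described as targets to be judged at each look.

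On planning, the section says "we conducted a series of simulations with effect sizes at the minimal value of the above criteria", and lists these as d = 0.1 for diet and activity and "1.1 incidence rate ratios for alcohol and 1.1 ORs for smoking". The result given is roughly 1500–2500 participants, repeated in the Abstract. The section adds that the criteria, not the simulations, will decide.

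Under Models, each primary outcome is analysed only in participants who met that behaviour's own inclusion criterion at baseline.

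**The concern.** Two features of the projection sit badly together.

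First, the simulated effects lie on the decision threshold. The second part of the effect criterion asks only that the posterior median exceed 0.10. If the truth is 0.10, the estimate falls on either side about equally often however much data there are, so the probability at a single look levels off near one half.

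Second, the rule is joint. Even if each cell has a good chance of having met a criterion by some N, 60 cells together may have almost none.

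The projection is the only planning figure in the article, and the 12-month recruitment period is stated alongside it. If the stated rule would hardly ever release the trial in that range, the actual stopping point will be set by judgement or resources, and readers will have been given the wrong expectation.

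**Working it through.** **Inputs from the protocol.** Criteria, priors, looks every 50, half the sample on each component, six components, five primary measures (two alcohol, one diet, one activity, one smoking), and follow-up at 2 and 4 months. Simulated effects are 0.10 and ln(1.1) = 0.0953.

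**Assumed, because the article does not give them.** SE = c/√N, where N is the number analysed. c = 2 for an unadjusted standardised outcome; 1.4 to 2 is the main range. Correlation between the two time points is 0.7 to 0.95. Errors are independent across components (the factors are balanced) and across outcomes.

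**Step 1: single look, one coefficient, c = 2.** The 97.5% part is the binding one until 1.96 × 2/√N = 0.10, that is N = (1.96 × 2/0.10)² = 1537. Futility also first becomes attainable at about that N. Probability of meeting any criterion:

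| True effect | N=500 | 1000 | 1500 | 2000 | 2500 | 10,000 |
|---|---|---|---|---|---|---|
| 0.10 | 0.20 | 0.35 | 0.49 | 0.54 | 0.55 | 0.55 |
| ln(1.1) | 0.18 | 0.32 | 0.45 | 0.51 | 0.51 | 0.49 |
| 0.15 | 0.39 | 0.66 | 0.83 | 0.87 | 0.90 | 0.99 |
| 0 | 0.05 | 0.05 | 0.05 | 0.45 | 0.62 | 1.00 |

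From about 1500 upward, more data do not settle a single look at the simulated effects. They do at 0.15 or at zero.

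**Step 2: looks every 50, one coefficient, c = 2 (20,000 runs).** At a true 0.10, the chance that some criterion has been met by N is about 0.67 at 1500, 0.80 at 2000 and 0.85 at 2500. The 75th and 80th percentiles of the stopping N are about 1750 and 2000. This is the nearest match to the published range. Exact reproduction is not possible without the simulation inputs and the target stopping probability.

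**Step 3: the stated rule, 6 × 5 × 2 = 60 cells, everyone in every analysis set (1,000 runs per setting).** Chance that every cell has met a criterion at some look:

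| c | Time correlation | by 1500 | by 2500 | by 5000 | by 10,000 |
|---|---|---|---|---|---|
| 2 | 0.7 | 0.000 | 0.000 | 0.04 | 0.27 |
| 2 | 0.95 | 0.000 | 0.001 | 0.05 | 0.34 |
| 1.4 | 0.7 | 0.000 | 0.009 | 0.18 | 0.54 |
| 1.4 | 0.95 | 0.001 | 0.034 | 0.23 | 0.56 |

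If all cells must be satisfied at the same look, no run succeeded up to 10,000.

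**Step 4: how far correlation between outcomes could help.** If all outcomes and both times moved in perfect step, only six independent components would remain. The ceiling by 2500 would be 0.854⁶ = 0.39 for c = 2 and 0.933⁶ = 0.66 for c = 1.4. Different behaviours measured in different subsets cannot be near that limit.

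**Step 5: subsets.** With assumed shares of 0.9 (diet), 0.6 (activity), 0.4 and 0.6 (the two alcohol measures) and 0.25 (smoking, 20% quit rate), no run of 400 at either correlation met all cells by 10,000. Smoking is the tightest. SE of the log OR is 2/√(N·p(1−p)), so 1.96 × SE = ln(1.1) requires N = (1.96 × 2/0.0953)²/(p(1−p)). That is about 18,800, 10,600 and 8,100 baseline smokers for assumed quit rates p of 10%, 20% and 30%.

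**The case against.** The strongest reply is that this is a sequential design, so a fixed-look probability is the wrong yardstick. That is right, and it disposes of a reading a reader might be tempted by: that meeting a criterion is a coin flip at every N, so 1500–2500 could not have come from these simulations. Below about 1500 a single look does worse than a coin flip. With repeated looks, the cumulative chance for one coefficient keeps rising, and its upper percentiles fall inside the published range.

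A reader might also make much of the ratio of 1.1, since ln(1.1) = 0.0953 lies inside the futility interval and on the harm side for alcohol. Neither point drives N. exp(0.10) = 1.105, so 1.1 is probably rounding. The effect and harm criteria and the priors are symmetric about zero, so 1.1 and 1/1.1 give the same stopping N in this approximation. What remains is a labelling fault.

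It is also fair that the final size is not fixed in advance, that the criteria are targets, and that an article may leave simulation inputs to a fuller document. This limits the consequence, but it does not align the published range with the rule printed beside it.

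**Conclusion.** The point holds as a mismatch between the projection and the stopping rule. At the simulated effects, 1500–2500 is plausible for one standardised coefficient, while the stated 60-cell rule would be satisfied by 2500 with probability about 0 to 0.03, and by 10,000 about 0.3 to 0.6.

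This rests on a normal approximation, c between 1.4 and 2, time correlation between 0.7 and 0.95, and independent errors across outcomes. Positive correlation between outcomes would raise the joint figure. Baseline-criterion subsets and loss to follow-up would lower it. The documents do not support the further inference that the simulations were wrongly computed, because their inputs and the unit they refer to are not shown. The point should be corrected, but it does not undermine the conduct of the trial.

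**What to change.** - Simulate the joint rule over all 60 cells with outcome-specific analysis sets, for a grid of true effects that includes zero and values on both sides of 0.10 (for example 0, 0.05, 0.10, 0.15 and 0.20, in both directions).
- Replace the 1500–2500 statement, in the Sample size section and the Abstract, with the resulting distribution of N and the stopping probability. Alternatively, restate it explicitly as a per-coefficient figure with its stopping probability.
- State whether a criterion must hold at the look when recruitment stops or need only have been met once.
- As a minor labelling correction, give the alcohol and smoking ratios with signs that match the criteria. Benefit for alcohol is a negative coefficient, so the minimal ratio is exp(−0.10) = 0.905. For smoking, say whether abstinence or smoking is modelled. The listed outcome is abstinence, for which an OR of 1.1 is a benefit, yet the criteria count a positive smoking coefficient as harm.

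The cost is a simulation re-run and a short table. Nothing in the conduct of the trial needs to change.

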**Methods and analysis:**

The effects of six components of a novel digital multiple health behaviour change intervention on alcohol consumption, diet, physical activity and smoking (coprimary outcomes) will be estimated in a factorial randomised trial. The components are designed to facilitate behaviour change, for example, through goal setting or increasing motivation, and are either present or absent depending on allocation (ie, six factors with two levels each). The study population will be those seeking help online, recruited through search engines, social media and lifestyle-related websites. Included will be those who are at least 18 years of age and have at least one unhealthy behaviour. An adaptive design will be used to periodically make decisions to continue or stop recruitment, with simulations suggesting a final sample size between 1500 and 2500 participants. Multilevel regression models will be used to analyse behavioural outcomes collected at 2 months and 4 months postrandomisation.

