## Introduction

Behavioural risk factors, such as harmful alcohol consumption, unhealthy diets, insufficient physical activity and smoking, contribute to about one-third of global disability-adjusted life-years, and are leading causes of non-communicable diseases (NCDs), including cardiovascular disease, respiratory disease, cancer and diabetes.^1 2^ The WHO has determined that reducing the prevalence of behavioural risk factors should be a priority in many societies to reduce the incidence of NCDs and disability-adjusted life-years.^3^ It is therefore important that effective and scalable means of helping individuals to improve their health behaviours are established.

The Public Health Agency of Sweden’s national public health survey from 2020^4^ (n=16 947) reports data on lifestyle behaviours of Swedish citizens aged 16–84. According to the survey, 16% of respondents report hazardous or harmful alcohol consumption, 35% report being insufficiently physically active, 12% report smoking occasionally or daily and 93% report eating less fruit and vegetables than recommended. Additionally, 52% of individuals report being obese or overweight. Unfortunately, with the exception of smoking, the prevalence rates of these behaviours have not decreased markedly over the past 10 years, with some increasing, witnessing of a lost decade for prevention efforts.

For prevention efforts to have an impact on the general population, they need to have extensive reach among those who may benefit. No single setting will be able to achieve this, for example, only 1%–5% of individuals visiting primary healthcare clinics in Sweden are given advice with respect to their lifestyle,^5^ despite many more in need of such advice. Unhealthy lifestyle behaviours also tend to cluster and interact,^6 7^ for example, those who are overweight are more likely to be physically inactive, and excessive alcohol consumption may lead to weight gain. Risks from multiple unhealthy lifestyle behaviours may be multiplicative^8^; thus, it is of value to not only extend the reach of interventions, but to also investigate tools designed to support change of multiple health behaviours.

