## Methods

A double-blind factorial randomised trial^17^ (six factors with two levels each) will be employed to address the objectives of the study. A Bayesian group sequential design will be employed to periodically make decisions to continue or stop recruitment.^18–20^ This protocol contains relevant items from the Standard Protocol Items: Recommendations for Interventional Trials.^21^ The methods of this trial, including the statistical analysis plan, was preregistered on the Open Science Platform prior to enrolment commenced (https://osf.io/xyj3p/).

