##### Primary outcome measures

Alcohol: Weekly alcohol consumption; monthly frequency of heavy episodic drinking.Diet: Average daily consumption of fruit and vegetables.Physical activity: Weekly MVPA.Smoking: Four-week point prevalence of smoking abstinence.

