### Models

#### Primary and secondary outcomes

Analyses of primary outcomes will be conducted among those fulfilling the respective criteria for inclusion at baseline, for example, weekly alcohol consumption will be analysed among those who reported having consumed 10/15 (female/male) or more units of alcohol the past week. BMI, sugary drinks, candy/snacks, QoL and perceived stress will be analysed among all participants, and number of cigarettes smoked weekly among baseline smokers.

Weekly alcohol consumption, frequency of heavy episodic drinking per month, weekly intake of candy and snacks, number of sugary drinks per week and cigarettes smoked per week are all count variables that are likely skewed and over dispersed. Therefore, these outcomes will be analysed using negative binomial regression. If found not to be over dispersed, we will consider using normal regression (possibly log transformed). Average intake of fruit and vegetables per day, MVPA minutes per week, BMI, QoL and perceived stress will be analysed using normal regression (possibly log transformed). Point prevalence of smoking abstinence will be analysed using logistic regression.

All models will be adjusted for age, sex and mediators (importance, confidence and know-how) at baseline. Primary outcomes and perceived stress will be adjusted for their respective baseline values, except for smoking prevalence which will be adjusted by the weekly number of cigarettes smoked at baseline. BMI, sugary drinks and candy/snacks will be adjusted for baseline MVPA minutes per week and average intake of fruit and vegetables per day. Number of cigarettes smoked last week will be adjusted by its baseline value. QoL will be adjusted for perceived stress at baseline.

In addition to pairwise interactions between components, effect modification will be explored in all models to assess if any of the baseline characteristics moderate the effects of the components of the intervention.

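### The stated stopping rule cannot be expected to resolve smoking at 1500–2500 participants, so the sample-size forecast and the full-power claim do not match the rule

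*Protocol article*

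**What the plan says.** The Methods section describes a factorial trial with "six factors with two levels each". There are five primary outcome measures, because alcohol supplies two ("Alcohol: Weekly alcohol consumption; monthly frequency of heavy episodic drinking") alongside fruit and vegetables, moderate-to-vigorous activity and smoking abstinence. The abstract says the models use "behavioural outcomes collected at 2 months and 4 months postrandomisation".

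The Sample size section sets effect, harm and futility criteria for each component's coefficient, per outcome and follow-up. Effect and harm need more than 97.5% posterior probability on the sign and more than 50% beyond 0.10 in the same direction, under a N(0, 1) prior. Futility needs more than 95% posterior probability between −0.10 and 0.10 for every outcome, under a normal prior with SD 2. Only outcomes analysed by normal regression are standardised. The rule is then: "We will continue recruitment until one criterion is fulfilled for each component, for each outcome, at each follow-up interval".

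On size: "Simulations suggested that approximately 1500–2500 participants will be necessary to recruit". The simulations used d = 0.1, incidence rate ratios of 1.1 and odds ratios of 1.1. The section adds that the criteria, not the simulations, settle the final number. It also claims full power for each contrast because "half the study population are given access to each individual component".

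Under Models, however: "Analyses of primary outcomes will be conducted among those fulfilling the respective criteria for inclusion at baseline". Smoking abstinence is analysed by logistic regression.

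**The concern.** The forecast and the power claim are argued from everyone recruited, while each outcome is analysed only in those at risk on it at baseline. The same ±0.10 futility margin also applies to a standardised mean difference and to a raw log odds ratio. The second carries far less information per participant.

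If the rule cannot resolve smoking at the forecast size, three things follow. The published expected sample size describes a different, weaker condition from the one stated. Recruitment would have to end by judgement rather than by the criteria. And the section's assurance that the futility criteria will pick up a component that does not work for a given outcome would fail for one of the coprimary behaviours.

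**Working it through.** **Inputs.** From the protocol: 6 components, 5 primary outcomes, 2 follow-ups, 1:1 split per component, 0/1 dummies, the thresholds and priors above, logistic regression for smoking, simulated odds ratio 1.1. Not in the protocol, so shown as ranges: abstinence at follow-up (p) and the share of participants who smoke.

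**Number of coefficients.** 6 × 5 × 2 = 60, of which 6 × 2 = 12 concern smoking.

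**Precision that futility needs.** In the most favourable case the posterior is centred exactly at 0. Then the posterior SD must be at most 0.10/1.96 = 0.0510. Posterior precision is 1/0.0510² = 384.15. Subtracting the prior's 1/2² = 0.25 leaves 383.90 to come from the data.

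**Trying to reproduce 1500–2500.** For a standardised normal outcome Var(ß) = 4/n, so n = 4 × 383.90 ≈ 1,536 analysed participants before futility is possible. If baseline explained 25% of the variance (an assumption), this is 0.75 × 1,536 = 1,152. Similarly, d = 0.1 has 50% power at 1,537 and needs 3,140 for 80%. So the lower end of the range matches one normal contrast in everyone recruited. The range was not reproduced for the rule as written.

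**Smoking, futility route.** Var(ß) = 4/[n p(1−p)], so n = 4 × 383.90/[p(1−p)]:

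| Abstinence p | Followed-up smokers needed |
|---|---|
| 50% | 6,142 |
| 30% | 7,312 |
| 20% | 9,597 |
| 10% | 17,062 |

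These are floors, since any estimate away from zero needs more. At 50% abstinence, 6,142 smokers means about 12,300 followed-up participants if half smoke (6,142/0.50), 24,600 if a quarter do (6,142/0.25), and 51,000 at 12% (6,142/0.12). The 12% is the general-population figure in the Introduction ("35% report being insufficiently physically active, 12% report smoking occasionally or daily"). The trial's own share is not given.

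**Best case at the forecast size.** Suppose every participant smokes, half abstain and none are lost.
- At 2,500: SE = 4/√2500 = 0.080. The largest possible futility probability is 2Φ(0.10/0.0799) − 1 = 78.9%.
- At 1,500: SE = 4/√1500 = 0.103. The maximum is 66.8%.

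Neither can reach 95%, whatever the data show.

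**Smoking, effect route.** At SE 0.080 with the N(0, 1) prior, the estimate must exceed 0.157 in size, an observed odds ratio of about 1.17. With a true log odds ratio of ln 1.1 = 0.095, the probability is 1 − Φ((0.157 − 0.095)/0.080) ≈ 0.22. At 1,500 it is 0.15. With 300 smokers (12% of 2,500, as an illustration) it is 0.055, and the observed odds ratio must be about 1.6. Note also that 0.095 lies just inside the ±0.10 futility zone.

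**Joint condition.** A simulation took looks every 50 participants up to 2,500, with an assumed correlation of 0.6 between a component's two time points, 50% abstinence and odds ratio 1.1. With everyone a smoker, all 12 smoking coefficients met a criterion at the same look in 0 of 4,000 runs. If a criterion counts once met at any look, the figure was 0.075%, and 0% when half, a quarter or 12% smoke. For comparison, a normal outcome analysed in all 2,500 met its own 12 criteria at the same look in about 1% of runs, and in 18–19% if met at any look.

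**The case against.** The strongest reply is that the section calls the criteria targets and leaves each interim decision to the team's judgement, and that 1500–2500 is a forecast in a design with no fixed size. This stands against one tempting inference: that recruitment would never stop. The documents do not support that, because discretion is written in and about 12 months of recruitment is anticipated. It does not rescue the forecast. The next sentence makes recruitment continue until every criterion is met, the following paragraph says the criteria decide, and the forecast is presented as what the simulations of those criteria gave.

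Second, the full-power sentence answers the worry that 64 conditions fragment the sample. That is right as far as it goes, and randomisation should give roughly an even split within each at-risk subgroup too. But an even split within a subgroup does not supply the subgroup's numbers.

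Third, a reader might apply the survey prevalences to the trial and conclude that most outcomes are too small. The documents do not support this either. Those figures describe the general population, the trial recruits online help-seekers with at least one unhealthy behaviour, and the same survey reports 93% below the fruit and vegetable recommendation. The smoking result does not depend on any share, since it holds even if everyone smokes.

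Fourth, a component with a large smoking effect could meet the effect criterion with far fewer smokers. True, but all six would need such effects at both times, and the simulated odds ratio is 1.1.

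Finally, posterior probabilities, medians and intervals are reported for each coefficient of interest whether or not a criterion is met. So the analysis itself is not invalidated. The forecast, the power claim and the stated rule are what fail.

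**Conclusion.** Wrong as written. For smoking, the stopping rule and the 1500–2500 forecast cannot both stand. Futility needs at least about 6,142 followed-up baseline smokers, roughly 2.5 times the upper end of the forecast even if every participant smoked (6,142/2,500 = 2.46). The futility probability is capped at 79% at 2,500 and 67% at 1,500. The effect route gives about 22% per coefficient at best at the simulated odds ratio, with 12 coefficients to resolve.

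This rests on the usual large-sample variance of a log odds ratio, a 1:1 split, the stated priors and the ±0.10 margin applying on the log-odds scale, as the text implies. Unknown smoker share, abstinence rate and attrition can only make it worse. For the normal outcomes the claim is weaker: 1,536 analysed participants (fewer if baseline explains variance) is within reach for one contrast if the at-risk subgroup is large enough, but the joint condition remains unlikely. The two alcohol outcomes were not quantified here.

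**What to change.** 1. Re-run the simulations with the rule as written: at-risk subgroups, attrition, and the joint condition over all 60 coefficients allowing for correlation. State whether criteria must hold at the same look or may be met at any look.
2. Replace the 1500–2500 statement by the expected precision, and the probability of meeting a criterion, for each outcome at the planned size.
3. Limit the full-power statement to the outcomes and subgroups where the re-run shows that it holds, and qualify the sentence saying that futility will capture ineffective components.
4. Reconcile the sentence calling the criteria targets with those that make them binding. Say that recruitment may end at a stated size or date, and that coefficients meeting no criterion will be reported as inconclusive.

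The cost is a simulation re-run, revised text and less favourable stated figures. No extra participants are needed.
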